### Recruitment {15}

We will sample a homogenous population group (obese patients with body mass index (BMI) from 30 to 50 kg/m^2^), thus reducing the standard deviation and hence the sample size. We will recruit 100 obese patients (50 patients in two groups).

## Assignment of interventions: allocation

### Sequence generation {16a}

Informed consent will be obtained from each participant before patient enrollment in the study. Patients who meet all of the inclusion criteria and none of the exclusion criteria will be consecutively included and randomized into one of the two study arms by the study statistician, who is not involved in the enrollment, assignment, or assessment of patients, according to a random allocation sequence generated by Stata 7.0. The randomization list is kept strictly confidential. Allocation concealment is ensured by using sequentially numbered, identical, opaque, sealed envelopes (*n* = 100). Patients will be randomized to one of two groups at a 1:1 allocation ratio.

### Concealment mechanism {16b}

Sealed envelopes will be used during the visit before surgery.

### Implementation {16c}

The intervention will be communicated to the patient by a nurse who has no involvement in the enrollment or assessment of patients and who will open the sealed envelope during the visit before surgery.

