### Trial design {8}

The study was designed as a single-center prospective, interventional, randomized controlled trial. Masking: None (Open Label) Allocation: randomized. Enrollment: 100 obese patients.

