### Eligibility criteria {10}

Inclusion criteria:
Obese patients had a body mass index (BMI) from 30 to 50 kg/m^2^.The patient is generally fit for anesthesia (ASA grading 1–2) and surgery.The patient commits to the need for long-term follow-up.

Exclusion criteria:
Patients with superobesity—BMI more than 50 kg/m^2^.Prosthetic (mesh) Hiatal herniorrhaphy or large hiatal herniaEsophageal shorteningLos Angeles Classification of Esophagitis (LA grade) C or D reflux esophagitisHistory of surgery on the stomach or esophagusLess than 18 or more than 60 years of ageNot fit for bariatric surgeryPsychiatric illnessPatients unwilling or unable to provide informed consent

The drop out criteria:
Refusal to participatePatient not available for long-term follow-up

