#### Participant timeline {13}

The flow diagram of the study design is shown in Table 1.

**Table 1 Tab1:** The schedule of enrollment, interventions, and assessments of the FundoRingMGB trial

	Study period					
	Enrollment	Allocation	Post-allocation			Close-out
**Timepoint**	**V1 (preoperative)**	**V2 (operation)** ***March–December 2021***	**V3 12 months**	**V4 24 months**	**V5 36 months**	**April 2024**

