### Plans to promote participant retention and complete follow-up {18b}

Data collection begins on the day a participant signs the informed consent form and continues until the termination of the trial or until the participant withdraws from the trial for any reason. If participants discontinue or deviate from the study protocols, the investigators will attempt to minimize the missing data. All original data are kept in chronological order for verification.

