### Methods in analysis to handle protocol nonadherence and any statistical methods to handle missing data {20c}

Randomized clinical trials analyzed using the intent-to-treat (ITT) approach provide unbiased comparisons between treatment groups. In cases of nonadherence, intent-to-treat analysis will be performed to avoid overlap and exclusion effects that could disrupt the random assignment of treatment groups in the study. The ITT analysis will provide information on the potential effects of treatment policies rather than on the potential effects of a particular treatment.

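### The text opens the envelope at a visit before surgery, but Table 1 marks allocation only at the operation visit; if the earlier time is meant, patients can withdraw after learning their arm

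*Protocol article*

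**What the plan says.** All places are in the Protocol article.

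- **Concealment mechanism {16b}:** "Sealed envelopes will be used during the visit before surgery".
- **Implementation {16c}:** a nurse with no part in enrolment or assessment tells the patient the arm, and it is this nurse "who will open the sealed envelope during the visit before surgery".
- **Participant timeline {13}, Table 1:** V1 is the preoperative visit and stands under Enrollment. V2 is the operation and stands under Allocation, with the period March to December 2021. The allocation row is blank at V1 and has its only mark at V2. V2 also carries marks for BMI and GERD symptoms.
- **Trial design {8}:** "Masking: None (Open Label) Allocation: randomized".
- **Eligibility criteria {10}:** two drop-out criteria, which run together in the text: "Refusal to participatePatient not available for long-term follow-up". Neither is tied to the time before or after randomisation.
- **Plans to promote participant retention {18b}:** data are collected to the end of the trial or "until the participant withdraws from the trial for any reason". The next sentence says that the investigators will try to limit missing data when a participant discontinues or deviates.
- **Handling of nonadherence and missing data {20c}:** "In cases of nonadherence, intent-to-treat analysis will be performed".

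**The concern.** The moment at which the arm becomes known is a key event in a randomised trial, and the article appears to place it at two different times. A site following {16b} and {16c} would disclose the arm before the operation visit. A site following Table 1 would do so at that visit.

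The earlier time is the weaker choice. One arm adds an experimental wrap of the fundus and the other is the standard operation, so patients may react differently to the two results. Someone who learns the arm and then leaves the trial before surgery is a loss after randomisation whose cause can depend on the arm. Such losses erode the comparability that randomisation creates.

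**Working it through.** **1. Timing, side by side**

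| Source | When the arm is revealed |
|---|---|
| {16b} and {16c} | at a visit before surgery |
| Table 1, V1 (preoperative) | no allocation mark |
| Table 1, V2 (operation) | the only allocation mark |

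There are two readings. If the pre-surgery visit is V1 or another visit before V2, the text and the table conflict. If it is the first part of V2, they agree in substance and only the wording is loose. The article does not say which. The separate preoperative column favours the first reading. The BMI and GERD-symptom marks at V2 allow the second, since they imply a patient encounter beyond the operation itself. Visit labels are not reliable elsewhere either: {18a} numbers the 24- and 36-month visits V3 and V4, where Table 1 has V4 and V5.

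**2. What happens to a patient who leaves in the interval**

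Under {10} a refusal is a drop-out, and under {18b} collection stops at withdrawal. A patient who withdraws fully before surgery therefore contributes no BMI or endoscopy at 12, 24 or 36 months. Intention to treat under {20c} keeps patients in their allocated arm, but it cannot supply outcomes that were never collected.

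**3. Possible size**

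The article gives no drop-out rate and no interval, so there is no figure of its own to reproduce. Inputs:
- n = 50 per arm ({15}).
- Assumed: k = 2 to 5 patients leave one arm after disclosure and none leave the other.
- Assumed: those who leave would have differed from those who stay by δ = 0.5 to 1 SD in the BMI outcome.

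Shift of the arm mean, and so of the contrast = (k/50) × δ:
- smallest: (2/50) × 0.5 = 0.02 SD
- largest: (5/50) × 1 = 0.10 SD

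Standard error of the contrast at 50 per arm = √(1/50 + 1/50) = √(2/50) = 0.20 SD. The largest shift is 0.10/0.20 = half a standard error.

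Effect on two-sided type I error when 5 of 50 (10%) leave one arm: SE = √(1/45 + 1/50) = 0.2055 SD, and the error is Φ(−1.96 + b/SE) + Φ(−1.96 − b/SE) for a shift b:
- b = 0.05 SD (δ = 0.5): 5.7%
- b = 0.10 SD (δ = 1): 7.8%

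**4. Against the planned effect**

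Sample size {14} assumes a difference of 15 with SD 10, which is 15/10 = 1.5 SD. The largest shift above is 0.10/1.5 = 6.7% of that.

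**The case against.** The strongest reply is that nothing here has to conflict. Table 1 can be read as a phase chart: V2 spans the whole recruitment period and includes assessments, so a nurse could open the envelope at an encounter within V2 and satisfy every section. This stands as a possible reading. A reader might infer a proven contradiction, and the article does not support that. It supports an inconsistency on a plain reading that needs one clarifying statement.

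Second, a reader might infer that everyone who refuses the allocated operation is lost and that intention to treat fails for all of them. That is too strong. A patient can decline the allocated procedure, stay in the trial and still be weighed and examined. Sections {18b} and {20c} cover that patient. Only full withdrawal loses the data.

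Third, the interval could be hours, in which case moving the envelope changes little. This also stands, since no length is given.

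Fourth, patients know their arm in any open-label trial, and concealment up to the opening is sound: consent comes first, the envelopes are numbered, opaque and sealed, and the nurse has no part in enrolment or assessment. The point is therefore not a failure of concealment. What survives is narrower: disclosure before the day of surgery would add an avoidable opportunity for arm-dependent withdrawal before any treatment is given.

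**Conclusion.** The point holds as a conditional one. On a plain reading, {16b} and {16c} disagree with Table 1 about when the arm is revealed, unless the pre-surgery visit is part of V2. If the envelope is opened at an earlier visit, full withdrawal after disclosure is possible, can depend on the arm, and is beyond the reach of the intention-to-treat analysis.

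The size is unknown. The range of 0.02 to 0.10 SD rests wholly on the assumed number of losses, their confinement to one arm, and the assumed outcome difference. Even its upper end is small against the planned 1.5 SD effect. It would matter more if the true difference between arms were much smaller than planned. The article gives no basis for saying that the comparison will be biased, only that the earlier timing allows it. This is a worthwhile, inexpensive improvement, not a threat to the trial's validity.

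**What to change.** Reconcile {16b} and {16c} with Table 1. The preferred wording has the same nurse open the next numbered envelope at V2, on the day of surgery, after the patient has consented to either procedure and eligibility has been finally confirmed. The sequence, envelopes and staff stay as they are. If the pre-surgery visit already falls within V2 on that day, a sentence saying so is enough.

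The cost is small but not nil: a short amendment, and the theatre team and the patient learn the procedure only that day. The benefit is limited in two ways. Under Trial status, recruitment began in March 2021 and was expected to end in December 2021, so the change helps only patients not yet randomised. It also does nothing about drop-out during the three years of open-label follow-up.

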## Assignment of interventions: blinding

### Who will be blinded {17a}

We will use an open-label trial, or open trial, when a type of clinical trial in which information is not withheld from trial participants. Bath, our open-label trial, is still randomized.

### Procedure for unblinding if needed {17b}

Not applicable.

## Data collection and management

### Plans for assessment and collection of outcomes {18a}

Treatment-related data were collected at V1 (baseline). According to the study protocol, follow-up data will be collected from V2 to 12 months, 24 months (V3), and 36 months after surgery (V4) (Table 1).

### Plans to promote participant retention and complete follow-up {18b}

Data collection begins on the day a participant signs the informed consent form and continues until the termination of the trial or until the participant withdraws from the trial for any reason. If participants discontinue or deviate from the study protocols, the investigators will attempt to minimize the missing data. All original data are kept in chronological order for verification.

### Data management {19}

Original data are transferred in a timely manner to a paper-based case report form (CRF) and an electronic database system located in a guarded facility at the trial site. Access to the study data is restricted. The PI will have access to the final dataset. An independent steering committee will monitor and examine adherence to the study protocol.

### Confidentiality {27}

The relevant regulations of the data protection legislation will be maintained.

The participants’ confidentiality was maintained at all times. For confidentiality reasons, case report forms (CRFs) do not contain any personal data on study participants. Members of the ethics committees are obliged to respect confidentiality and to refrain from divulging the participants’ identities or any other personal information they might be aware of. Source data in the hospital’s electronic patient information systems are secured by personal passwords and medical secrecy is maintained.

### Plans for collection, laboratory evaluation, and storage of biological specimens for genetic or molecular analysis in this trial/future use {33}

Not applicable.

## Statistical methods

### Statistical methods for primary and secondary outcomes {20a}

Statistical analysis will be performed using Microsoft Excel for Mac (Microsoft Corp., Redmond, WA) and StatPlus: MacPro (AnalystSoft Inc., Walnut, CA).

The normal distribution of the variables will be tested using the Kolmogorov–Smirnov test. Subsequently, quantitative demographic and outcome variables will be reported as the means and standard deviations (SD); qualitative variables will be reported as counts and percentages. Between-group comparisons among quantitative variables will be performed using independent one-way ANOVA. Where ANOVA omnibus F test is significant, pairwise comparisons using Fisher's least significant difference (LSD) method will be performed. Between-group differences among qualitative variables will be assessed using the chi-square test or Fisher's exact probability test. Measures of within-group change in quantitative variables, from baseline out to 12, 24, and 36 months, will be analyzed using the dependent-samples *t* test. Correlation and linear regression analyses will be performed to assess the strength and direction of the relationship between changes in BMI and telomere length and to estimate the predictive value of BMI change relative to telomere length at the 12-, 24-, and 36-month follow-ups. Statistical significance was set at *p* < 0.05.

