### Outcomes {12}

#### Primary outcome measure

Change of body mass index: The measure assesses a change of body mass index. Weight (kg) and height (cm) will be combined with the body mass index (BMI) kg/m^2^. Time frame: Baseline at 12, 24, and 36 months after surgery. Ideal body weight was calculated as 25 × [patient’s height in meters]^2^. Effectiveness endpoint follow-up included body mass index (BMI, kg/m^2^), change in BMI (ΔBMI [initial BMI − postoperative BMI]), excess BMI loss (EBMIL, % [(ΔBMI/initial BMI − 25) × 100]), and total weight loss (TWL, % [initial weight − postoperative weight/initial weight × 100]).

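### The arms are compared on BMI with an unadjusted one-way ANOVA (plus a redundant LSD step) that leaves out baseline BMI as a covariate and uses only patients seen at each visit, so precision is lost and the ITT statement is not met for patients lost to follow-up

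*Protocol article*

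**What the plan says.** The primary outcome is change in BMI, defined under Primary outcome measure as "change in BMI (ΔBMI [initial BMI − postoperative BMI", with BMI itself, excess BMI loss and total weight loss alongside. The timing reads "Time frame: Baseline at 12, 24, and 36 months after surgery". Table 1 schedules BMI at the preoperative visit for every patient.

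For the analysis, section {20a} states: "Between-group comparisons among quantitative variables will be performed using independent one-way ANOVA". When the omnibus F test is significant, "pairwise comparisons using Fisher's least significant difference (LSD) method will be performed". Change within each arm, "from baseline out to 12, 24, and 36 months, will be analyzed using the dependent-samples *t* test". No baseline covariate and no repeated-measures term is named. Linear regression appears only for BMI change against telomere length.

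Section {10} makes being unreachable for long-term follow-up a drop-out criterion. Section {20c}, whose heading also covers missing data, states: "In cases of nonadherence, intent-to-treat analysis will be performed to avoid overlap and exclusion effects". The trial has two arms of 50, allocated 1:1.

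**The concern.** An omnibus F test followed by pairwise LSD is built for three or more groups. Here it tests one comparison twice.

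The more useful point is what the test leaves out. Eligible BMI runs from 30 to 50 kg/m², and a patient's starting BMI is likely to predict the later value. A one-factor ANOVA has no place for it. The precision given up costs nothing to recover, because the covariate is already collected.

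The second issue is who enters the comparison. With three follow-up visits and no repeated-measures term, the ANOVA has to be run separately at each visit, on patients who have a value at that visit. (The protocol says so explicitly only for the paired t tests; for the ANOVA it follows from the method.) A patient seen at 12 and 24 months but not at 36 contributes nothing to the 36-month result. Weight regain is a target of the trial, and it could itself influence whether a patient returns.

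**Working it through.** **The plan's own figure.** With Zα = 1.96, Z(1−β) = 1.28, SD = 10 and d = 15 from section {14}: n = 2 × (1.96 + 1.28)² × 10² / 15² = 2 × 10.4976 × 100/225 = 9.33 per group, as printed. (1.28 is the value for about 90% power, while the text says 80%. That is a separate matter and nothing below depends on it.)

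**Is power at stake?** The standard error of an arm difference with 50 per arm is 10 × √(2/50) = 2.00. Then 15/2.00 − 1.96 = 5.54, so power exceeds 99.9%. If 20% were lost (an assumption), 40 per arm gives 10 × √(2/40) = 2.24 and 15/2.24 − 1.96 = 4.7, again above 99.9%. The difference detectable with 80% power is (1.96 + 0.84) × 2.00 = 5.60 with 50 per arm and 6.26 with 40. Both are far below 15.

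**LSD.** With two groups F = t², so the LSD test returns the same p value as the omnibus test.

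**Gain from adjustment.** Let ρ be the correlation of baseline with follow-up BMI. The documents do not give it, so 0.3 to 0.8 is assumed, with equal variances at both times. Relative to the variance of ANOVA on follow-up BMI (set to 1), ANOVA on change has variance 2(1 − ρ) and the adjusted analysis has 1 − ρ². The ratio of adjusted to change is therefore (1 − ρ²)/[2(1 − ρ)] = (1 + ρ)/2.

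| ρ | adjusted ÷ follow-up BMI, 1 − ρ² | adjusted ÷ change, (1 + ρ)/2 |
|---|---|---|
| 0.3 | 0.91 | 0.65 |
| 0.5 | 0.75 | 0.75 |
| 0.7 | 0.51 | 0.85 |
| 0.8 | 0.36 | 0.90 |

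On change in BMI the variance falls by 10 to 35%. Since √0.90 = 0.95 and √0.65 = 0.81, the confidence interval is about 5 to 19% narrower. On follow-up BMI the variance falls by 9 to 64%.

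**A second set of assumptions.** A simulation with baseline SD 4.5, mean total weight loss 25 to 35% and its SD 7 to 10 points (none of these is in the documents) has baseline BMI explaining 7 to 23% of the variance of change. Near the middle, 14.5% corresponds to 50/(1 − 0.145) = 58 effective patients per arm. With height constant, percent change in BMI equals percent total weight loss. If that is unrelated to baseline BMI, the explained share is 0 and adjustment gains nothing on that scale.

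**Incomplete follow-up.** This was simulated with 50 per arm, BMI SD 5, equal correlation ρ between all visits, no true effect, and about 21% missing at 36 months depending on 24-month BMI. The adjusted estimate is a likelihood-type estimate using all randomised patients.

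| Drop-out pattern | ρ | Bias, ANOVA on follow-up BMI (kg/m²) | Bias, ANOVA on change | Bias, adjusted |
|---|---|---|---|---|
| opposite direction by arm | 0.5 | 0.94 | 0.03 | 0.03 |
| opposite direction by arm | 0.7 | 1.28 | 0.01 | 0.02 |
| same direction in both arms | 0.5 | 0.03 | −0.01 | 0.00 |
| same direction in both arms | 0.7 | 0.02 | 0.01 | 0.01 |

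With same-direction drop-out the standard errors were 1.10 (follow-up BMI), 1.12 (change) and 0.96 (adjusted) at ρ = 0.5, and 1.09, 0.88 and 0.79 at ρ = 0.7.

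The absence of bias on change reflects the simulated structure. With equal variances and correlations, 36-month BMI and baseline BMI have the same covariance with 24-month BMI, so the change is uncorrelated with the variable that drives drop-out.

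**The case against.** Much can be said for the plan, and most of it stands.

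- An unadjusted comparison in a 1:1 randomised trial is valid. A reader might infer that the ANOVA result would be biased in general; with complete data it is not.
- A reader might infer that baseline is ignored altogether. It is not: the primary outcome is change from baseline, and excess BMI loss and total weight loss also use the starting value. The relevant gain is therefore the smaller one, against ANOVA on change.
- A reader might infer that the trial is underpowered. At the planned effect it is not.
- A reader might take the drop-out criteria to mean that such patients are removed from the analysis set. No section says so. The shortfall against ITT comes from tests that need a value at the visit.
- The within-arm t tests are described as measures of within-group change and are not offered as arm comparisons. LSD is redundant but harmless.
- The recruitment remark "We will sample a homogenous population group" is not shown to be wrong. Excluding BMI above 50 does narrow the range compared with unrestricted enrolment.
- Covariance structure, imputation and sensitivity analyses are details an article may leave to a fuller document, and their absence is not held against it here.

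What does not fall away is that the article itself fixes the between-arm test. That test has no covariate and cannot use a patient without a value at the visit.

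**Conclusion.** The point holds as an improvement in precision and as a mismatch between the fixed test and the ITT statement. It does not show that the planned comparison is invalid.

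On change in BMI, adjustment is worth a variance reduction of about 10 to 35%, given ρ between 0.3 and 0.8 and equal variances; under the second set of assumptions it is worth about 58 rather than 50 effective patients per arm. It may be worth nothing on percent change. The benefit lies in interval width and in differences well below the planned 15 points.

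On incomplete follow-up, sections {10}, {20a} and {20c} do not fit together for patients who stop attending. Bias of about 0.9 to 1.3 kg/m² appeared only for follow-up BMI with drop-out running in opposite directions by arm. None appeared for change in BMI in that structure, or for drop-out that was alike in both arms. The size therefore depends on the outcome scale and drop-out pattern, neither of which can be known now. If return depends on regain that is never observed, a mixed model does not remove the bias either.

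**What to change.** In section {20a}, replace ANOVA and LSD for the weight outcomes by a comparison adjusted for baseline BMI. The preferred form is a mixed model for repeated measures with arm, visit (12, 24, 36 months), arm-by-visit interaction and baseline BMI, analysing patients in their allocated arm with all data collected. Report the arm difference at 36 months with its 95% CI.

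The simpler form is ANCOVA (linear regression) at 36 months. It recovers the precision but still uses only patients seen then. In either form, a patient with no postoperative BMI adds almost no information, so the number of such patients should be reported by arm.

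Delete the LSD step and label the paired t tests as descriptive. Reconcile {10} with {20c} by stating that the data already collected from patients who drop out stay in the analysis.

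The cost is wording and slightly more analysis work, with no extra patients or visits. Section {20a} names Excel and StatPlus, and Stata 7.0 is named only for the allocation sequence, so the mixed model may need other software. The regression form should not, since {20a} already plans linear regression.
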